#### Strength and endurance measures

All strength and endurance measures take place in the same neuromuscular evaluation laboratory (Neuromuscular Physiology and Evaluation Lab, Institute of Myology, Pitié- Salpêtrière Hospital, Paris) by the same trained physiotherapist.

#### Pulmonary function and respiratory strength

For all respiratory evaluations, patients are seated with a backrest and feet firmly on the floor. Forced vital capacity (FVC) is measured with a Micro Medical Spiro USB spirometer and Spida 5 software or a Vitalograph spirometer (the same spirometer is used for all evaluations for each patient). Calibration is performed according to manufacturer’s guidelines with a 3-L syringe before each evaluation. FVC in litres is measured from total lung capacity according to the ATS/ERS task force guidelines [35]. Patients are instructed to inhale completely and then exhale maximally until no more air can be expelled. For respiratory muscle strength evaluations, the MicroRPM device (Micromedical, Rochester, UK) is used. Maximal inspiratory pressure (MIP) is measured first, followed by maximal expiratory pressure (MEP). Both are expressed in cmH_2_O. MIP is measured from residual lung volume and MEP from total lung capacity [36]. All measurements are repeated three times or until maximum values are reached if the patient continues to improve and remains clinically stable (no signs of fatigue). For MEP measures, patients are asked to place their hand around the mouthpiece to minimise air leaks. A tubed mouthpiece is used for both. Strong verbal encouragement is provided for all measures. A nose clip is used for FVC. The highest value from the three trials is used in data analysis. Secondary outcome measurements involve the mean change in FVC, MIP and MEP between M3 and M6.

#### Upper and lower limb strength and fatigue

Voluntary strength testing is performed using a Biodex System 3 Pro dynamometer (Biodex Medical Systems, Shirley, NY, USA). For the upper limb, elbow flexion force is evaluated. The patient is seated in the adjustable Biodex chair with the shoulder in 90° flexion and 15° horizontal abduction. The upper arm is placed on a support, the elbow flexed to 90° and the forearm in full supination, with the strap placed at the wrist, leaving the hand free. The axis of the dynamometer is aligned with the joint axis of rotation of the elbow. Bilateral shoulder straps and a waist strap are used to stabilise the thorax and pelvis to avoid compensations. For the lower limb knee extension force is evaluated with the patient seated in the Biodex chair with the hips and knees flexed to 90°. The thorax, pelvis and right thigh are secured with straps. The axis of the dynamometer is aligned with the axis of rotation of the knee. Both positions are designed to avoid the influence of gravity on the muscle contraction.

Before each test, there is one test trial at submaximal force to ensure that the patient understands the instructions. Testing involves three isometric contractions at maximal voluntary isometric force (MVIC) followed by a 1-min rest between each MVIC trial. Maximal torque is presented in Nm. The highest value from the three trials of each muscle group is used in data analysis. Following the third MVIC there is a 5-min rest period where the patient remains in the same position. Fatigue testing comprises a sustained 40-s isometric contraction at 50% of their best individual MVIC from the same day. A last MVIC is performed immediately after completing the fatigue exercise. Visual cues are provided to the patient via a computer screen to enable them to maintain the target level of force for the duration of the fatigue test. Strong verbal encouragement is provided by the evaluator for both force and fatigue testing. The details of the dynamometer position (chair position, height, depth, etc.) for each patient are noted for repeatability in successive testing. Measurements are performed on the right side only. Secondary outcome measure is the mean change in UL and LL strength between M3 and M6.

#### Electrophysiological measurements

Surface EMG (sEMG) is a non-invasive method of evaluating the electrical signals of muscles to gain insight into the physiological characteristics of a muscle contraction. It has been used to investigate peripheral muscle fatigue in various conditions [37, 38] Myoelectrical manifestations of fatigue can be studied during sustained submaximal contractions through changes in amplitude and frequency content of the sEMG signal. In this study, four aligned miniature, circular silver-silver chloride (Ag/AgCl) surface electrodes of 4 mm in diameter, 11 mm inter-electrode distance are used. Three signals are derived from this bipolar configuration. The electrodes are connected to an amplifier (bandwidth = 10–1000 Hz). Where necessary, hair is gently removed with a shaver and the skin is abraded slightly and cleaned with an alcohol solution to reduce inter-electrode resistance. To improve conduction electrolytic gel is placed on the electrodes which are then placed on the biceps brachii (BB) for elbow flexion and on the vastus lateralis (VL) for knee extension, parallel to the estimated direction of muscles fibres according to the Surface EMG for Non-Invasive Assessment of Muscles (SENIAM) recommendations [39]. A neutral reference electrode is placed on the ulnar styloid for the BB and the fibular head or patella for the VL.

Surface EMG recordings are performed for both force and fatigue tests at a sampling rate of 10 kHz and stored on the computer for further analysis. Surface EMG recordings will be processed using standard methods using the root mean square (RMS) as an estimate of the signal amplitude, notably indicating the level of motor unit recruitment during the contraction and the mean power frequency (MPF) as an estimate of the mean value of the power spectral distribution of the signal used to evaluate localised muscle fatigue. The onset of fatigue is identified by a decrease in the MPF. Where possible, muscle fibre conduction velocity will also be computed.

#### Grip strength

Handgrip strength of the dominant hand is measured via an isometric contraction using the Myogrip dynamometer (Ateliers Laumonier, France), an electronic device specifically designed to measure grip strength in neuromuscular disorders [40]. Its handle can be adjusted to accommodate different hand sizes and the strength is displayed directly on the screen. Patients are seated on the edge of a plinth, their back in an upright position, hips and knees flexed to 90° and feet flat on the floor. The dominant arm hangs down the side of the body with the shoulder in neutral and the elbow extended. The patient is instructed to squeeze the handle as hard as possible; verbal encouragement is provided to motivate the patient to perform a maximal effort. The test is performed three times or until no further improvement. Maximal grip strength is recorded in kg. Mean change in grip strength between M3 and M6 is a secondary outcome.

#### Walking endurance

Walking endurance is measured via the 6-min walk test (6MWT), a simple, well tolerated and reliable quantitative measure of functional exercise capacity [41]. Patients are instructed to walk the longest distance possible in 6 min in a 25 m long, level surface indoor corridor. At each end of the 25 m they turn around a cone placed on the floor. There is a starting line marked on the floor on the right of the first cone. Instructions provided before the test and verbal guidance throughout the test are standardised according to the American Thoracic Society guidelines/recommendations [42]. The total distance (m) is recorded (6MWD) as well as the time every 25 m. The patient is advised to wear comfortable walking shoes for the test. An accelerometer (Locometrix) is worn around the lumbar spine during the test for possible more in-depth gait analyses. Mean change in 6MWD between M3 and M6 will be evaluated as a secondary outcome.

As anticholinesterase inhibitors can temporarily influence muscle strength and fatigue the timing of medication is recorded as well as the timing of each evaluation. Where possible the same timing is respected for consecutive evaluations.

#### Free-living physical activity

Free-living physical activity and sedentary behaviour are quantitatively measured at four time points during the trial. Patients wear a tri-axial seismic accelerometer (DynaPort Movemonitor, McRoberts) on their lumber spine using the supplied elastic belt. The accelerometer weighs 55 g and measures 106.6 × 58 × 11.5 mm. It stores raw data on a microSD card and contains a USB connection to upload data to the software for preparation and analysis. The accelerometer measures acceleration in three axes at a sample rate of 100 samples per second. Algorithms developed by the manufacturer quantify physical activity and inactivity by measuring body posture and movement intensity from acceleration signals [43]. Body postures include lying/sitting/locomotion/standing and shuffling where shuffling is defined as < 3 consecutive steps or where the intensity or direction of motion doesn't comply with locomotion. Measurements begin at a pre-set time. Patients are instructed to wear the device during waking hours for seven consecutive days, except when bathing/showering or swimming. Multiple days are monitored to account for day-to-day variation.

Free-living physical activity is further evaluated via the completion of a Bouchard questionnaire at the beginning of the study [44]. The questionnaire enables an estimation of the daily energy expenditure over a three-day period by asking patients to record their physical activity over a 72-h period (two weekdays and one weekend day). The day is divided into 96 periods of 15 min and activities are quantified on a scale of 1–9 depending on their intensity. The questionnaire has the added benefit of providing a qualitative perspective on the activities performed which is lacking in the accelerometer data. Yet the accelerometer data, when worn correctly, lacks the problems of recall bias. Thus, the two can be considered complementary.

#### QOL and psychological state

At three, six and nine months anxiety is evaluated via the State Trait Anxiety Inventory (STAI) and depression is evaluated via the modified Beck Depression Inventory (BDI-13). Psychiatric disorders are evaluated by the Mini-International Neuropsychiatric Interview (MINI, French Version 5.0.0) and self-esteem via the Self-Esteem Inventory scale (SEI) at both three and nine months. Global QOL is measured via the World Health Organisation QOL-BREF scale and specific QOL via the MGQOL-15-F at zero, three, six and nine months. Semi-structured interviews are conducted at zero, three, six and nine months. We ask patients to draw themselves at zero, six and nine months. Evaluations are carried out during a face-to-face meeting with a clinical psychologist which lasts approximately 90 min. The mean change in the total score for each questionnaire will be compared between groups at M3 and M6 as secondary outcomes.

The STAI evaluates anxiety via a self-administered questionnaire consisting of two 20-item sub-scales: the STAI A evaluates the actual level of anxiety at the moment of the assessment (state anxiety); and the STAI B investigates more general and long-standing anxiety (trait anxiety) [45]. Scores are in the range of 20–80 for each questionnaire with higher scores indicating greater anxiety. The French version was validated by Bruchon-Schweitzer and Paulhan [46].

The SEI evaluates the judgment that an individual holds about themselves regardless of the circumstances. The self-administered questionnaire, adapted into French (ECPA, 1984), consists of 58 items with sentences describing feelings, opinions or individual reactions with either a ‘like me’ or ‘unlike me’ response [47]. It investigates self-esteem in four domains: personal (26 items); social (eight items); family (eight items); professional (eight items); and contains a lie scale (eight items). A higher score indicates greater self-esteem.

Depression is evaluated via the self-administered BDI-13 (short version), consisting of 13 items validated in French by Collet and Cottraux [48]. Each item has four response choices (0–3) and provides a global score (0–39) corresponding to depression severity (0–4 = no depression, 4–7 = mild, 8–15 = moderate, ≥ 16 = severe depression).

The MINI is a short, structured, clinical interview organised in diagnostic modules [49]. It enables researchers to investigate 16 axis I DSM-IV disorders according to the DSM-IV or the CIM-10. For most modules, two to four screening questions are used to rule out the diagnosis when answered negatively. Positive responses to screening questions are explored by further investigation of other diagnostic criteria. The MINI is also used to confirm the diagnosis of depression if the Beck score is ≥ 4.

Global QOL is evaluated by the WHOQOL-BREF [50]. The French translation was validated by Leplège et al. in patients with various neuromuscular diseases [51]. This self-administered questionnaire consists of 26 items (score of 0–5) and assesses QOL according to four domains: physical health; psychological health; social relationships; and environment. Myasthenia-specific QOL is evaluated by the French version of the Myasthenia Gravis QOL scale, the MGQOL-15-F as previously described (primary outcome measure) [31].

Semi-structured interviews are conducted by trained clinical psychologists to qualitatively assess the psychological impact of MG on patients’ personal, marital, social, professional life and physical activities. The interviews are recorded to be qualitatively analysed with the NVivo software 7 as it allows a thematic analysis [52]. Finally, patients are asked to draw themselves. The instructions are: ‘Can you draw yourself as you feel today?’ This drawing is analysed as a projective test and considered as an index of the representation of the body and of its investment [53].

### Other exploratory measures

#### Inflammatory and immunological markers

The level of pro- and anti-inflammatory cytokines is measured at three, six and nine months. A total of 50 mL of venous blood is collected and the serum and mononucleated cells are isolated. Blood samples of the same patients are operated simultaneously to avoid inter-experimental variability. The sera are conserved in a freezer at – 80 °C and the cytokines are analysed by ELISA or Bioplex technology. The cytokines to be studied in the sera include the interleukin (IL)-6, IL-17, IL-21, interferon gamma and tumour necrosis factor alpha (pro-inflammatory cytokines) as well as IL-10 and IL-1RA (anti-inflammatory cytokines) [54]. The mononucleated cells are isolated using a Ficoll gradient. The cells are frozen in a freezing medium containing 10% dimethyl sulfoxide. The phenotype of the monocytes and lymphocytes will be investigated by flow cytometry using a combination of eight markers. The expression of cluster of differentiation (CD)14 coupled with CD16 and Toll-like receptor 4 of the monocytes will be analysed [54]. We will also determine the proportion of regulatory B cells (Breg) and regulatory T cells (Treg) in the lymphocytes. The percentage of Treg cells will be determined using the combined expression of CD4, CD25, CD127 and FoxP3 (a marker associated with the regulatory function) on permeabilised cells (as the FoxP3 marker is intracellular). The percentage of Breg cells will be determined by the combination of CD19, CD38, CD27 and CD24. The expression of chemokine receptors such as CXCR3 (pro-inflammatory) and CXCR5 (follicular helper cells) will also be determined. The flow cytometry experiments will be performed on a FACSCanto (Becton-Dickinson) apparatus.

Levels of circulating specific MG antibodies (AChR or MuSK) are measured at inclusion, three, six and nine months.

### Adverse event reporting

An adverse event (AE) is defined as any untoward medical occurrence in a participant which does not necessarily have a causal relationship with this study. These can be identified at any moment during the study. Eligibility criteria rule out patients with known contraindications to physical exercise. An ECG is performed monthly to monitor cardiac status. It is expected that patients in the experimental group may experience muscle soreness and fatigue in response to exercise, particularly for the more sedentary patients. However, this is not an AE as it is considered a normal response to exercise.

A serious adverse event (SAE) includes: death; risk of death; necessity or prolongation of existing hospitalisation; persistent or significant disability or incapacity; or any other undesirable event considered to be medically significant. MG exacerbation requiring modification of current therapeutic management during the intervention period is considered a possible AE. All suspected unexpected SAEs are to be notified without delay to the sponsor, as well as any worsening of the disease suspected to be related to the physical programme if a patients' treatment needs to be modified. In this case, unblinding can occur. Should a worsening occur without needing a change of the treatment, it is only to be recorded in the electronic database without mandating a direct report to the sponsor. The sponsor’s vigilance unit is in charge of the causality assessment as well as of its regulatory duties with regard to reporting obligations to the French Medicines Agency.

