## Background

Auto-immune myasthenia gravis (MG) is a rare, chronic, auto-immune disease of the neuromuscular junction. The incidence is estimated to be 30 per 1,000,000 people per year worldwide [1]. MG affects both genders and symptoms include fluctuating fatigue and weakness which vary in intensity and location (upper and/or lower limbs, axial, eyes and face, bulbar and respiratory muscles) [2]. These symptoms affect patients to varying degrees and while disease-induced mortality is rare nowadays, activities of daily function are affected and quality of life (QOL) is reduced [3–6]. Relapses are unpredictable and can be present throughout the disease course, especially in the initial stages when the disease may not yet be treated. Current treatment includes various pharmacological agents which are either symptomatic such as acetylcholinesterase inhibitors which act to temporarily relieve symptoms or disease-modifying immunosuppressors aimed at minimising the auto-immune response. As there is currently no known cure, the goal of treatment is to obtain remission; and where this is not possible, to obtain disease stability with the least symptoms.

While rest is recommended during an acute exacerbation of MG, evidence is lacking as to whether exercise is both feasible and beneficial in periods of disease stability. Anecdotal evidence from patients with MG suggests that those who participate in regular physical exercise feel better. According to them, it gives them confidence in their capacities and helps them understand their disease and their personal limits. Some even report experiencing symptom improvement and reduced levels of fatigue [7].

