For the general population, it is widely accepted that regular physical exercise has multiple positive physical and psychological effects as well as being effective in the prevention of various non-communicable diseases such as stroke, heart disease and cancer and increasing longevity [8–10]. Recently, the use of exercise has been proposed in the management of various neurological diseases [11–13]. Exercise has even been compared to pharmacological treatment and has been found to be equivalent in some populations, supporting the recent notion that ‘exercise is medicine’ [14]. Traditionally, exercise was thought to exacerbate symptoms for patients suffering from MG as their muscle weakness and fatigue was thought to be brought on or worsened by physical exertion and improved with rest. Despite the increasing number of studies exploring exercise in various neuromuscular pathologies, to date, little research has explored physical activity in the context of MG [15, 16]. Several case studies exist which demonstrate that despite the disease patients can participate in sport and increase their strength, power or endurance with adequate training [17–20]. A within-subject control study provided promising results, yet these limited data do not enable us to draw reliable conclusions concerning the safety and benefits of physical exercise for patients with MG [21]. Two new studies provide further information including different types of physical exercise [22, 23]. In the study by Rahbek et al., progressive resistance training appears to be beneficial however aerobic training seems to increase depression and fatigue and reduce knee extensor strength [22]. The mixed aerobic resistance program study carried out by Westerberg improved functional physical performance and exercise self-efficacy without strength improvements noted [23]. Exercise was well tolerated in both studies; however, due to small sample sizes and lack of control group, it is difficult to make firm conclusions about the various possible benefits. It is hypothesised that physical exercise is beneficial for adults with stabilised MG.

The primary aim of this study is to determine whether a regular moderate intensity physical exercise program improves perceived QOL for patients with stable, generalised MG. Secondary aims are to evaluate the effects of this exercise program compared to usual care on physical fitness, depression and self-esteem as well as on the immune system.

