### Compliance to the physical exercise program

Compliance is calculated as the number of completed sessions compared with the number of intended sessions. Session duration and rowing distance are recorded for each session onto a card via the rowing machine monitor. In addition, patients are requested to fill in a training logbook to record medication and any minor adverse effects related to training sessions (such as fatigue or any MG symptoms). Patients are informed to contact their general practitioner if there is any worsening of symptoms and to inform the physiotherapist of the study. Compliance is facilitated by weekly phone calls to check on progress and provide encouragement. Reasons for non-compliance are noted. The rowing machine is collected at the end of the intervention period (i.e. M6). Factors preventing or limiting completion of the exercise program are noted such as absence, unrelated illness, etc.

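### Exercise-related fatigue and soreness are exempted from adverse event status in one arm only, against the protocol's own AE definition and its logbook section, which tilts AE counts towards exercise by an unknown amount

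*Protocol article*

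**What the plan says.** The section Adverse event reporting gives a broad definition: an AE is "any untoward medical occurrence in a participant which does not necessarily have a causal relationship with this study". A few sentences later it adds: "It is expected that patients in the experimental group may experience muscle soreness and fatigue in response to exercise", particularly the more sedentary ones, and concludes: "However, this is not an AE as it is considered a normal response to exercise". No limit of severity or duration is attached.

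The section Compliance to the physical exercise program asks patients who train to keep a logbook in which they "record medication and any minor adverse effects related to training sessions (such as fatigue or any MG symptoms"). No logbook is described for controls.

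The Background says of MG that "symptoms include fluctuating fatigue and weakness", and reports that in one cited exercise study "aerobic training seems to increase depression and fatigue and reduce knee extensor strength". It also says that exercise was well tolerated in both of the recent studies it describes, and that small samples and the lack of a control group prevent firm conclusions.

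The article's title and its Discussion name tolerance next to benefit as a question of the trial. Trial status reports 32 patients included and no exercise-related AEs so far.

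**The concern.** Whether an event was expected, and whether the intervention caused it, are attributes of an AE. Neither decides whether it is one, and the protocol's definition says as much about cause. The exemption uses both to take an event out of the definition, and does so for the experimental group only.

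Fatigue is a poor candidate for such treatment here. It belongs to the disease, and the article itself names it as a possible effect of aerobic training; the planned session has a 20-minute aerobic plateau. At stake is the meaning of the AE table and of any tolerance statement drawn from it. If exercise does cause troublesome fatigue, the rule removes that excess from the count.

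**Working it through.** **Placing the sections side by side**

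1. The general definition depends on neither cause nor expectedness. The exemption depends on both. They conflict within one section.
2. Training-related fatigue is a minor adverse effect in the compliance section and not an AE in the reporting section. Both labels cannot stand.
3. The exemption names the experimental group. A new or worse complaint of fatigue in a control patient falls under the general definition with no exemption.
4. The monthly assessor is a blinded neurologist, and patients are told not to reveal their allocation to that neurologist. An assessor who does not know the arm cannot apply a rule that depends on the arm. Any asymmetry must therefore arise when events are classified, not when symptoms are collected. Symptoms collected in the same way in both arms thus already exist.

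**What the rule does to a recorded comparison**

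The plan gives no AE rate, so there is no AE figure to reproduce. The only planned figure used is 21 patients per arm, from Sample size calculation. It reproduces: for a difference of 8 and an SD of 9, a two-sided 5% t-test with 80% power needs 20.87 per arm, rounded up to 21 (power 80.3%). It is not in dispute.

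Let pE and pC be the true risks of reportable fatigue or soreness in the exercise and control arms, and q the share of exercise-arm events that are exempted. All three are assumptions. If recording is otherwise the same in both arms:

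- recorded risk difference = pE × (1 − q) − pC
- true risk difference = pE − pC
- contribution of the rule = −q × pE, which is never above zero

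With equal true risks (pE = pC = p), so that the true difference is 0, and 21 patients per arm, the expected recorded events are:

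| p | q = 50%: exercise vs control | Difference (points) | q = 100%: exercise vs control | Difference (points) |
|---|---|---|---|---|
| 10% | 1.05 vs 2.1 | −5 | 0 vs 2.1 | −10 |
| 20% | 2.1 vs 4.2 | −10 | 0 vs 4.2 | −20 |
| 30% | 3.15 vs 6.3 | −15 | 0 vs 6.3 | −30 |
| 50% | 5.25 vs 10.5 | −25 | 0 vs 10.5 | −50 |

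The right-hand half is an outer bound. It needs every complaint among exercisers to be exempted, whereas the wording covers only those in response to exercise.

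**Perfect application does not rescue the rule.** Take assumed risks of 30% with exercise and 15% without, so that exercise causes the extra 15 points. If only the exercise-caused events were exempted, q would be 0.15 / 0.30 = 50%, and the recorded risks would be 15% vs 15%. The harm would vanish from the table. The sign would change only if 0.30 × (1 − q) < 0.15, that is q > 50%, which means that MG or background fatigue was also filed as a normal response to exercise.

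**The case against.** The other side has a good deal to say, and most of it narrows the point.

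- **The exemption is limited to fatigue and soreness in response to exercise.** A reader might infer that all fatigue in an exerciser is exempt while all fatigue in a control is an AE. The text does not say so. That control fatigue would be entered as an AE follows from the general definition but is not stated, and in a disease with fluctuating fatigue it may not always happen. This stands.
- **MG worsening is not lost.** A reader might infer that early worsening can simply be filed as normal. The same section treats an exacerbation that needs a change of management as a possible AE, sends suspected programme-related worsening with a treatment change to the sponsor, and has worsening without a treatment change recorded in the database. The monthly history covers MG behaviour and muscle pain in both arms. What remains is the boundary between post-exercise fatigue and mild worsening. The article states no rule for it; the full protocol may, so the lack of detail is not itself the finding.
- **No between-arm test of AEs is described**, and the article ties tolerance partly to session data. MG scores, strength and a fatigue test are also measured in both arms. The bias therefore concerns AE counts and statements built on them, not every measure of tolerance.
- **The cited aerobic study is weak evidence of harm**, given the caveats in the Background. It shows that fatigue is plausible as an effect, no more.
- **A reversed direction cannot be claimed.** A reader might infer from the 30% and 15% example that the rule turns about 6 vs 3 affected patients into 0 vs 3. That takes unsourced rates and total exemption.

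None of this removes the conflict between the two sections or the rule that applies to one arm.

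**Conclusion.** The point holds in a limited form. The protocol contradicts itself on whether training-related fatigue is an adverse effect, and it exempts fatigue and soreness in response to exercise in one arm against its own definition. The rule can only lower the exercise-arm AE count, so AE counts and AE-based tolerance statements are tilted towards exercise. This assumes that fatigue and soreness are otherwise recorded alike in both arms.

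The documents do not allow the amount to be computed; the range of 5 to 25 points with half of the events exempted rests wholly on assumed values. The Trial status statement on exercise-related AEs has to be read with the exemption in mind, but nothing shows how many complaints, if any, were set aside. The primary outcome is not touched. This should be fixed before the analysis, but it does not threaten the trial's main result.

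**What to change.** - Reconcile Adverse event reporting with the compliance section by deleting the one-arm exemption.
- Classify fatigue, soreness and MG worsening under a single AE definition in both arms, using the monthly blinded neurologist history that is already scheduled. Record severity, expectedness and relatedness as separate fields, and tabulate by arm.
- Report the training logbook only as a description within the exercise arm. It offers up to 36 × 21 = 756 planned sessions at which an exerciser can note a complaint and has no counterpart in controls. Feeding it into AE counts would bias ascertainment against exercise.
- For patients already enrolled, reclassify events from the monthly histories only, not from the logbooks.

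The cost is a short amendment and some case report form wording. The downside is more non-serious AE entries and an AE table that looks less favourable to exercise.
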